Multicenter recruitment will allow for a more precise assessment of the effects of VT-ART, with the aim of demonstrating that implementing such a procedure is both feasible and safe among centers. Moreover, it will increase the chances to recruit patients with profiles matching the ones in the arm undergone VT-ART.

A standardized data collection has been defined for data regarding both VT-ART and RFA.

The trial will thus both collect prospective and retrospective data about VT-ART (following the predefined standardized data collection). Prospective data collection will be applied within the consortium for the patients referred to VT-ART after the beginning of the trial; retrospective data collection will be allowed for the VT-ART procedure delivered before the formal start of the trial if the data required by the predefined standardized data collection are available for defining the primary and secondary endpoint (see following sections). Similarly, prospective and retrospective data collection will be allowed for data about conventional treatment (i.e., RFA).

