## Populations

Our aim is to enroll patients with structural heart disease, in whom the presence of a myocardial scar induces refractory monomorphic VT or ventricular fibrillation (VF), as documented by either implantable cardioverter defibrillator (ICD) appropriate shocks or anti-tachycardia pacing (ATP) at ICD interrogation. We will enroll patients with recurrent VT/VF episodes despite optimal medical therapy (i.e., class III antiarrhythmic drugs) and at least one previous attempt of RFA or patients in whom ablation is not feasible, because of contraindications to the procedure or of patient intolerance. Previous percutaneous stellate ganglion blockade is neither a requirement for inclusion criteria nor exclusive criteria that will be collected in the standardized data collection for potential subgroup analysis.

Eligibility criteria are summarized in Table 1.

**TABLE 1 T1:** Inclusion and exclusion criteria.

Inclusion criteria	1. Patients with structural heart disease and monomorphic VT refractory to optimal medical therapy and previous RFA attempts (minimum of one attempt RFA)
	2. Patients with contraindications to conventional ablation or not suitable for any non-interventional approach, refusing any surgical ablative attempt; or patients who have already undergone RFA with arrhythmogenic focus refractory to previous ablation procedures
	3. Age >18 years
	4. Candidates not suitable for heart transplantation

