Our trial will combine two IGRT procedures to increase safety: intra-fractional and inter-fractional motion management devices and procedures are mandatory to be used. Volumetric imaging (CBCT- or MR-guided) scans before delivering each PA with regard to inter-fractional monitoring. Intra-fraction monitoring through the gating system is also mandatory. Continuous intra-fraction monitoring through an optical surface monitor system (OSMS) will be applied if available (e.g., TrueBeam Edge Linac, Varian Medical Systems, Palo Alto, CA, USA). Online adaptive procedures will be applied for the MR-guided Linac.

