#### Sample size

The calculation of the sample size considered followed assumptions:

-A total of 95% confidence level;-The drop-out rate of 10%;-Expected difference between the two treatments for 3-month and 6-month VT burden in terms of overall response rates: 20% higher in arm including VT-ART compared to the control group;-Power of 80%.

To improve clinically adequate balancing, we will enroll two matching paired patients in the group not undergoing VT-ART for each patient who undergoes VT-ART in a 2:1 ratio, favoring a larger proportion of patients not undergoing the innovative procedure (i.e., VT-ART).

Under these hypotheses, to detect a 20% improvement in the VT burden control rate in the VT-ART group vs. the control group, we calculated the sample size (in a 2:1 ratio) upon enrolling 149 patients: 100 in the non-exposed control group and 49 in the VT-ART group. Progressively, on a multicentric basis supervised by the promoting center in the VT-ART consortium, for each VT-ART patient enrollment, a matched pair patient profile according to the predefined features will be shared with the consortium to enroll two similar patients who have not undergone VT-ART. For enrollment into the control group, recruitment of clinical cases from retrospective case series within the multicentric consortium will also be allowed, with the only condition to be not earlier than 5 years from the enrollment of the matched pair patient in the VT-ART group (to avoid the possible influence of a too early approach for standard procedures).

All statistical analyses will be performed using SPSS^®^ version 25.0 software (©Copyright IBM Corporation 1994, 2017).

Due to the potential difficulty of enrolling the patients through the complete match of all matching factors, a protocol rule will be applied through patient’s collection.

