### Registration

The trial is promoted by Fondazione Policlinico A. Gemelli IRCCS, Rome (Italy). The clinical and investigational procedures will be based on approval from the local ethics committee. Each interested center will submit the protocol to its ethics committee for approval before accrual. After approval, the center will receive a dedicated electronic case report form (CRF). Eligible participants who provide consent and meet the inclusion criteria are anonymously registered in the CRF by assigning a numerical code. Final stratification of the enrolled patients will be performed globally to enhance the homogeneity and balance of the final dataset.

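### No stated rule requires consecutive or outcome-blind entry of retrospective patients, so both groups can be selected on a result the centre already holds

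*Protocol article*

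**What the plan says.** **VT-ART group.** On past procedures the Protocol overview states: "retrospective data collection will be allowed for the VT-ART procedure delivered before the formal start of the trial if the data required". The data meant are those that define the primary and secondary endpoints. The condition is thus that the endpoint information is already on record.

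**Control group.** The Sample size section states: "For enrollment into the control group, recruitment of clinical cases from retrospective case series within the multicentric consortium will also be allowed". The limit that it sets on such cases reads: "with the only condition to be not earlier than 5 years from the enrollment of the matched pair patient in the VT-ART group". The Protocol overview and Methods/design describe the search: the VT-ART patient's profile is circulated, and centres look for two similar patients who did not have VT-ART. The Abstract adds that this retrospective selection takes place at each centre on its own.

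**Other entry rules.** The Populations section points to a full list of criteria ("Eligibility criteria are summarized in Table 1"), with no exemption for past patients. The Registration section states: "Eligible participants who provide consent and meet the inclusion criteria are anonymously registered in the CRF". Controls must match on the Table 2 factors. If accrual on all factors falls short, the Sample size section falls back to the mandatory factors only.

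**Analysis.** The Follow-up section restricts the final analysis to patients with data at the follow-up time points. The Sample size section plans subgroup analyses by matching mode (all factors or mandatory only). It plans none by retrospective or prospective entry.

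**The concern.** The comparison is not randomised, so its validity rests on who enters. For a retrospective patient, the centre that proposes the case holds the outcome at that moment. In the VT-ART group, having the outcome is itself the entry condition. If a centre has more eligible past VT-ART patients than it submits, or more than two RFA patients who fit a profile, the stated rules do not say which ones enter.

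Selection related to outcome biases cardiovascular survival, event-free survival and VT burden alike. Matching does not remove it, because it acts within strata of the matching factors. It need not be deliberate: cases that are better documented or better remembered may also be those with particular results. Once enrolment has closed without a list of eligible patients who were not entered, the bias can be neither measured nor corrected.

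**Working it through.** **1. Does any stated rule close the gap?**

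| Rule | Where | What it does | Does it fix the choice among eligible past patients? |
|---|---|---|---|
| Eligibility | Table 1 | Narrows the pool | No |
| Consent and inclusion criteria | Registration | Condition for CRF entry | No |
| Matching, all or mandatory factors | Table 2, Sample size | Narrows the control pool | Not where more than two patients fit |
| Endpoint data available | Protocol overview | Puts the outcome on file before entry | No |
| 5-year window | Sample size | Limits the age of controls | No |
| Supervision by the promoting centre | Sample size | Concerns enrolment and sharing of profiles | Not stated to be outcome-blind |
| Global final stratification | Registration | Acts on patients already enrolled | No |

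**2. How large could the effect be?** The plan gives no figure for this, so what follows is an illustration. Inputs from the Sample size section are 49 VT-ART patients, 100 controls and a planned difference of 20%, read as 20 percentage points. Assumed inputs are the true VT control rate *p*, equal in both groups; the share *o* of past VT-ART failures left out; the retrospective share *s* of the VT-ART group; and unselected controls.

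- Apparent rate among retrospective VT-ART patients: *p* / (*p* + (1 − *p*)(1 − *o*))
- False difference: *s* × (apparent rate − *p*)

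With *p* = 0.5:
- *o* = 1/4: 0.5 / (0.5 + 0.5 × 0.75) = 0.571, an excess of 7.1 points
- *o* = 1/2: 0.5 / (0.5 + 0.5 × 0.50) = 0.667, an excess of 16.7 points

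| Failures left out | Half of group retrospective | All of group retrospective |
|---|---|---|
| 1 in 4 | 3.6 points (18% of the planned 20) | 7.1 points (36%) |
| 1 in 2 | 8.3 points (42%) | 16.7 points (83%) |

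**3. False-positive rate.** Use a two-sided 5% normal test, 49 against 100, with no true difference. For 1 in 2 left out and half retrospective, the VT-ART rate is 0.583 and the pooled rate is (49 × 0.583 + 100 × 0.5)/149 = 0.527. The standard error is 0.0871 under the null and 0.0864 otherwise. The upper tail is Φ((0.0833 − 1.96 × 0.0871)/0.0864) = Φ(−1.01) ≈ 0.156. The lower tail adds about 0.002, giving about 16%. The same steps give about 49% if the whole group is retrospective. With milder selection (1 in 5 left out, half retrospective) the false difference is 2.8 points and the rate about 6%.

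**4. Sensitivity to *p*.** With 1 in 2 left out, the false difference (half / all retrospective) is 8.6 / 17.1 points at *p* = 0.4 and 7.5 / 15.0 at *p* = 0.6. The plan states no control rate. With a two-sided test and 10% dropout, a total near 149 arises only at control rates of about 0.10 or 0.72. There the bias is smaller:
- *p* = 0.10: 0.10/(0.10 + 0.90 × 0.5) = 0.182, so 4.1 / 8.2 points
- *p* = 0.72: 0.72/(0.72 + 0.28 × 0.5) = 0.837, so 5.9 / 11.7 points

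**The case against.** **The article is condensed.** Tie-breaking, masking and screening logs often sit in a full protocol or CRF manual, and retrospective entry is an openly declared design choice. This lowers confidence that the gap exists in practice. But the point does not rest on missing detail alone: the article fixes an entry rule that makes a known outcome the condition for entry, and it places the search for controls with the centres that hold the outcomes. A better rule is available at little cost.

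**Discretion over controls may be small.** Matching on all Table 2 factors is demanding, and the plan itself expects too few matches: it has a fallback and a closure rule below 1:1. This stands in part. Where matches are scarce there is little to choose from. The fallback to mandatory factors widens the choice again, and scarcity of controls does not limit selection among past VT-ART cases.

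Four stronger readings are tempting, and the document does not support them:

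- *That data availability and the 5-year window are the only entry rules.* Eligibility, consent and matching also apply. The phrase about the only condition is most naturally an extra condition for using old case series.
- *That the window misaligns treatment eras.* It runs from the VT-ART patient's enrolment. Methods/design speaks of enrolment to undergo VT-ART, which would tie it to the procedure. For a past procedure the term could also mean registration. If, say, VT-ART was given 4 years before registration, control procedures could run from 1 year before it to 4 years after it. The text is ambiguous, and misalignment is not shown.
- *That past procedures outside the protocol's delivery rules will be counted.* The Radiotherapy section says "Intra-fraction monitoring through the gating system is also mandatory" and does not limit this to prospective patients. The retrospective entry rule does not mention it. These passages need reconciling, but no error is shown.
- *That modest selection yields a third or more of the planned effect.* At an assumed 50% control rate, leaving out 1 in 4 failures gives 36% only if the whole VT-ART group is retrospective. With half retrospective it gives 18%.

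**Conclusion.** The point holds in this form: eligibility, consent, matching, data availability and the 5-year window govern entry, but no stated rule requires consecutive or outcome-blind entry of retrospective patients. Both groups can therefore be selected on outcome, and the planned subgroup split would not reveal it. A reader might infer that centres will pick favourable cases. The document does not show that; it shows that the design permits it and could not detect it.

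At an assumed true control rate of 50% and with unselected controls, leaving out 1 in 4 to 1 in 2 past VT-ART failures gives a false difference of 3.6 to 8.3 points with half the group retrospective, and 7.1 to 16.7 points with all of it. The size depends on the retrospective share, the selection and the control rate, none of which the article gives. Selection among controls could add to it. The illustration concerns VT control, on which the sample size is based. No figure is offered for cardiovascular survival, the primary outcome, although the same mechanism applies.

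**What to change.** 1. Each centre lists all consecutive eligible VT-ART procedures from its first one, and all eligible RFA patients in the window, with baseline matching variables only.
2. The promoting centre selects controls by a prespecified matching rule before any outcome field is opened in the CRF.
3. State whether the 5-year window runs from procedure date or registration date. Procedure to procedure is preferable, so that treatment eras align.
4. Report results in the matched sets with a prospectively enrolled VT-ART patient as a sensitivity analysis.
5. Reconcile the retrospective entry rule with the Radiotherapy section, so that it is clear whether the delivery requirements apply to past procedures.

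The cost is a protocol amendment, a change in the order in which CRF fields open, and extra listing work at the centres. The sample size need not change.

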## Populations

Our aim is to enroll patients with structural heart disease, in whom the presence of a myocardial scar induces refractory monomorphic VT or ventricular fibrillation (VF), as documented by either implantable cardioverter defibrillator (ICD) appropriate shocks or anti-tachycardia pacing (ATP) at ICD interrogation. We will enroll patients with recurrent VT/VF episodes despite optimal medical therapy (i.e., class III antiarrhythmic drugs) and at least one previous attempt of RFA or patients in whom ablation is not feasible, because of contraindications to the procedure or of patient intolerance. Previous percutaneous stellate ganglion blockade is neither a requirement for inclusion criteria nor exclusive criteria that will be collected in the standardized data collection for potential subgroup analysis.

Eligibility criteria are summarized in Table 1.

**TABLE 1 T1:** Inclusion and exclusion criteria.

Inclusion criteria	1. Patients with structural heart disease and monomorphic VT refractory to optimal medical therapy and previous RFA attempts (minimum of one attempt RFA)
	2. Patients with contraindications to conventional ablation or not suitable for any non-interventional approach, refusing any surgical ablative attempt; or patients who have already undergone RFA with arrhythmogenic focus refractory to previous ablation procedures
	3. Age >18 years
	4. Candidates not suitable for heart transplantation

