## Aims

Our trial aims to assess the benefits of VT-ART for the ablation of VT in patients with optimized medical therapy in whom traditional techniques, namely, RFA, have either failed to control VT recurrence or cannot be performed.

The importance of our trial relies on the identification of new management options for patients who have not responded to traditional ablation techniques or have contraindications to invasive procedures. The efficacy of VT-ART will be indirectly compared through matched pair analysis with a population of patients not treated with VT-ART, thus avoiding setting a randomized controlled trial that is considerable technically demanding and possibly premature in this research field.

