## Methods/design

Our trial will investigate the effects of administering a single fraction of external beam radiation delivered through SBRT techniques at a dose of 25 Gy on patients with recurrent episodes of VT and in whom optimal medical therapy and previous RFA attempts have failed to provide benefit from VT burden control. We will perform matched pair analysis with dynamic cohorts. We will compare two groups of patients: One that has been treated by all the standard approaches but has not undergone VT-ART and a second group that has also received VT-ART. The entire enrolled group (by multicentric recruitment) will be stratified according to some predefined characteristics and analyzed by matched pair analysis, based on the characteristics of patients treated with VT-ART. Once a patient is enrolled to undergo VT-ART within the multicentric consortium, the search for two patients with similar feature profiles not undergoing VT-ART will be shared.

Matching factors taken into account are summarized in Table 2.

**TABLE 2 T2:** Applied matching factors.

Parameter type	Subgroup options
Etiology of cardiomyopathy*	ICM
	NICM
	ACM
Age*	
Gender*	
BMI	
LVEF*	
NYHA group*	
Ventricular arrhythmia presentations*	Sustained ventricular tachycardia incessant sustained ventricular tachycardia electrical storm
Arrhythmogenic focus anatomical intracardiac location	Based on VE exit by ECG and by the activation map of VT
Diagnostic tools used for scar definition	CT
	MR
	EAM
	ECG
TA volume*	Endocardial electroanatomic substrate mapping area/volume in all cases; epicardial mapping area/volume in the case of 3D epicardial electroanatomic substrate mapping
Heart volume	cc range
Heart-to-TA volume	cc range
Previous use of amiodaron	Y/N
Number of previous RFA attempts*	
Type of previous RFA attempts	endocardial
	epicardial
Unfeasibility to repeat RFA	Y/N
Local recurrence of TA (same area of last RFA)	Y/N
Previous percutaneous stellate ganglion blockade	Y/N

TA, target area by electroanatomical mapping; BMI, body mass index; RFA, radiofrequency ablation; LVEF, left ventricle ejecting fraction; *mandatory matching factor.

Figure 1 depicts the design of the VT-ART study.

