## Outcome measures

The primary outcome is investigating the difference in overall cardiovascular survival among the group undergoing VT-ART and the one not exposed to the innovative procedure.

The primary efficacy endpoint is a statistically significant difference in overall cardiovascular survival between the group undergoing VT-ART and the one not exposed to the innovative procedure; this will be defined in months and calculated from the time of the last procedure (represented by the last RFA for the control group and VT-ART for the innovative one, respectively).

The secondary outcome is evaluating the difference in ventricular event-free (referred to VT/VF, appropriate shock or ATP as recorded by the ICD) survival after the last procedure between the two groups (i.e., the single or last RFA in the control group and VT-ART in the innovative group). The respective endpoint is a statistically significant difference in ventricular event-free survival (in months) after the last procedure between the two groups.

An additional secondary aim is to evaluate the reduction in the number of VT episodes compared to the pre-treatment period between the two dynamic cohorts that will be investigated.

Ventricular tachycardia recurrence will be defined as evidence of monomorphic VT at ICD interrogation (either self-limiting or terminated by appropriate shock therapy or ATP). The number of VT episodes, defined as VT burden, in the 3 months before and after the procedure will then be compared.

The respective secondary endpoint will be evaluated facing 3 months before the last procedure (i.e., either RFA or VT-ART) and 3 months after.

We did set a blanking period after VT-ART before evaluate the effect on VT burden; in a recent study by Kautzner et al., the authors supported the pre-clinical theorem of myocardial apoptosis (up to 3 months post-stereotactic ablation) followed by a creation of fibrotic lesion (6–9 months post-stereotactic ablation) in the irradiated region (5). Consequently, we propose a 3-month-blanking period after the procedure.

Since a blanking period of 3 months after the procedure will be applied, the secondary endpoint will evaluate the number of VT episodes interval accounted for the last 3 months before the procedure and of the 3–6 months after it.

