### Statistical considerations and sample size for matched pair analysis

A descriptive analysis will summarize the total number and stratification of patients with RFA and VT-ART.

We will perform a comparative analysis between RFA and VT-ART in patients with structural heart disease and refractory VT. Each patient who will be treated by VT-ART will be compared with two patients in the control group treated with RFA and best standard care but without VT-ART, on the basis of the following matching factors: Etiology of cardiomiopathy (ICM, NICM, and ACM), ventricular arrhythmia presentations (sustained ventricular tachycardia; incessant sustained ventricular tachycardia; and electrical storm), diagnostic tools used for scar definition (CT, MR, EAM, and ECG), arrhythmogenic focus anatomical intracardiac location (on the basis of VE exit by ECG and by activation map of VT), TA volume (endocardial electroanatomic substrate mapping area/volume in all cases; and epicardial mapping area/volume in case of 3D epicardial electroanatomic substrate mapping), heart volume, heart-to-TA volume, rate number of previous RFA attempts, type of previous RFA attempts (endocardial and epicardial), time (in days) between the first RFA attempt and VT-ART, time (in days) between the last RFA attempt and VT-ART, previous percutaneous stellate ganglion blockade, time (in days) between the percutaneous stellate ganglion blockade and VT-ART previous use of amiodaron, NYHA group, LVEF, BMI, age, and gender.

As mentioned, applied matching factors are summarized in Table 2.

Continuous data will be expressed as mean ± standard deviation, as appropriate, for all variables collected from the entire population or specific subgroups. A comparative analysis for subsequent levels of qualitative variables through the chi-square test and quantitative variables (scores on quality of life) with the *T*-test will be performed.

Non-parametric tests will be provided where the population distribution does not have a known form (normal Gaussian).

The differences in baseline and follow-ups between the same group will be analyzed with repeated measures approach: using the Friedman test and MANOVA for continuous variables and McNemar or Cochran’s *Q*-tests for categorical ones.

The significance of the tests is fixed with *p* < 0.05.

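### Eligibility conflicts on whether a previous RFA is required; if never-RFA patients are admitted, the RFA-defined control group holds no comparable match for them

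*Protocol article*

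**What the plan says.** **Previous RFA required.** Table 1 item 1 (Populations) asks for disease refractory to medical therapy and to RFA, with a "minimum of one attempt RFA". Methods/design likewise describes patients in whom earlier RFA did not help.

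**Previous RFA not required.** The Populations text admits patients with "at least one previous attempt of RFA or patients in whom ablation is not feasible". Table 1 item 2 opens with "Patients with contraindications to conventional ablation or not suitable for any non-interventional approach" and offers this as an alternative to having already had RFA. Aims covers patients in whom traditional techniques "have either failed to control VT recurrence or cannot be performed". Protocol overview says the same.

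**Controls.** Statistical considerations pairs each VT-ART patient with "two patients in the control group treated with RFA and best standard care but without VT-ART". Under Outcome measures, the clock for cardiovascular survival starts at the last procedure, "represented by the last RFA for the control group and VT-ART for the innovative one". The ventricular event-free endpoint uses the same origin.

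**Matching.** Table 2 makes the number of previous RFA attempts mandatory. It also lists "Unfeasibility to repeat RFA" (Y/N), without the asterisk that marks a mandatory factor. The Sample size section allows matching on mandatory factors alone if control accrual falls short.

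**The concern.** Two issues follow from each other. First, centres cannot tell from the text whether a patient who never had RFA may enter, so they could enrol different populations under one protocol.

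Second, if such patients do enter, the control group is built around a procedure they could not have. Every control underwent RFA at time zero, whereas the never-RFA patient was judged unable to. The reasons for that judgement may be related to cardiovascular survival, the primary endpoint. Protocol overview itself gives the mix of patients who had RFA and patients unable to have it as a reason why balanced randomised arms would be hard to define. Matching does not remove that difficulty unless it deals with feasibility.

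**Working it through.** **Step 1. Can the eligibility statements be read together?** Table 1 numbers its inclusion criteria without an "or" between items, so the usual reading is that all apply. A patient who meets item 1 (refractory to at least one RFA) then already meets the second branch of item 2, and item 2 adds nothing. Its contraindication branch can never admit a patient without RFA. Yet the Populations text, Aims and Protocol overview all say such patients are intended. No single reading satisfies every statement.

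**Step 2. What happens to a never-RFA patient under each reading?**

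| Reading | Index RFA of a control | Result for a never-RFA VT-ART patient |
|---|---|---|
| Item 1 governs | not relevant | Not enrolled; no comparability problem |
| Permissive | Counts as a previous attempt | Controls have at least 1 attempt, the patient has 0: no match on a mandatory factor |
| Permissive | Does not count | Can match a control at a first RFA (0 before 0); that control was able to have RFA |

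The article does not say which counting rule applies. The third row confounds feasibility with treatment. The second loses patients but compares no unfit patient with a fit one.

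**Step 3. Is there another control?** Protocol overview and Methods/design describe controls more loosely, as not having had VT-ART. Neither gives a time zero for a control without RFA, so such a control could not enter the survival comparison as defined.

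**Step 4. Do the matching factors repair this?** "Unfeasibility to repeat RFA" presupposes an earlier RFA, is not mandatory and is missing from the list in Statistical considerations. Type of previous RFA (Table 2) and days since the first or last RFA (Statistical considerations) also separate never-RFA patients under full matching, but they have no value for such a patient. None of these survives the mandatory-only fallback.

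**Step 5. Size, for illustration only.** The documents give no never-RFA share f, so 10% to 30% is an assumption. VT-ART patients left = 49 × (1 − f), with two controls each. VT-ART enrolment needed to keep 49 matchable = 49 / (1 − f), rounded up.

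- f = 10%: 44.1, so 44 + 88; need 55
- f = 20%: 39.2, so 39 + 78; need 62
- f = 30%: 34.3, so 34 + 68; need 70

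The plan's total of 149 cannot be reproduced uniquely, because the control rate of VT burden control is missing. With 10% versus 30%, two-sided 0.05, 80% power and 2:1, the pooled formula gives 132, and 132 / 0.90 = 147 after dropout; other control rates give other totals.

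Power = Φ[(d − 1.96 × se0) / se1], with d = 0.20 (absolute, assumed), se0 from the pooled rate and se1 from the separate rates. Example, 49 + 98 at 10% versus 30%: pooled rate 24.5/147 = 0.167; se0 = 0.0652; se1 = 0.0721; (0.20 − 0.1278) / 0.0721 = 1.00; power 0.84.

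| Control rate | 49+98 | 44+88 | 39+78 | 34+68 |
|---|---|---|---|---|
| 10% | 0.84 | 0.80 | 0.76 | 0.70 |
| 25% | 0.69 | 0.64 | 0.59 | 0.53 |
| 50% | 0.64 | 0.59 | 0.54 | 0.48 |
| 65% | 0.74 | 0.69 | 0.63 | 0.57 |
| 75% | 0.90 | 0.86 | 0.80 | 0.74 |

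These figures concern VT burden control, the endpoint on which the sample size rests. They take no dropout off and ignore the matching. The article gives no power for cardiovascular survival.

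**The case against.** The best defence is that the two halves are alternatives. If item 1 governs, no never-RFA patient is enrolled and only a wording fault remains. That stands: the comparability problem is conditional. It still matters, because the permissive reading is the one stated in Aims.

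A second defence is that matching gives real protection. NYHA group, LVEF, age and arrhythmia presentation are mandatory factors. NYHA IV is excluded, and life expectancy above one year apart from VT is required. The Sample size section also promises separate analyses of patients matched on all factors and on mandatory factors only. This is true, and it limits the harm. But none of these measures feasibility of RFA, and the subgroup analysis could expose a problem without curing the whole-group result.

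A reader might go further and infer that the bias runs against VT-ART, because patients unfit for RFA are sicker. The documents do not support a direction. Populations also mentions patient intolerance, and the Discussion names difficult anatomical location, neither of which has to mean worse survival. A reader might also infer that the fallback drops the only factor separating these patients. It does not: type of previous RFA and days since RFA separate them too under full matching.

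**Conclusion.** The eligibility contradiction is established from the text and needs no assumption. The comparability problem holds if never-RFA patients may enter. It then takes one of two forms, set by an unstated counting rule: no match, or a match to a patient able to have RFA. Both cannot be asserted for the same patient, and in the second form the direction of confounding is unknown.

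The documents do not allow the size to be estimated. The range of 5 to 15 patients out of 49 follows only from the assumed 10% to 30% and should not be read as a forecast. The point matters whatever the share, because it decides who belongs in the primary comparison.

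**What to change.** 1. Reconcile Aims, Protocol overview, the Populations text, Table 1 and Methods/design into one rule on previous RFA. Which rule is the sponsor's decision.
2. State whether a control's index RFA counts towards the mandatory number of previous attempts.
3. If never-RFA patients stay eligible, run the primary matched comparison in VT-ART patients with at least one previous RFA, and report never-RFA patients descriptively. Covariate adjustment is no substitute: with every control RFA-treated, there is no overlap to adjust over.
4. Separately, among patients with a previous RFA, keep "Unfeasibility to repeat RFA" in the mandatory-only fallback or adjust for it. This does not solve the never-RFA problem. Confirm that the item is collected, since Table 2 lists it but the list in Statistical considerations does not.

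**Cost.** Items 1 and 2 are wording. Item 3 leaves fewer VT-ART patients in the primary comparison: about 34 to 44 of 49 under the assumed share, or 55 to 70 enrolled to keep 49. The power statement should be redone for the number expected to remain. Item 4, if done by matching, makes controls harder to find.
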